**5.2 Quantitative Data Analysis**

Baseline characteristics of the study participants will be summarized using descriptive statistics. Continuous variables will be summarized using the mean, median, standard deviation, interquartile range, and range. Discrete variables will be summarized using frequencies and percentages.

The primary analysis will be a comparison between groups of breastfeeding rates at 3 months using Fisher's exact test. All tests will be two-sided, with p-values less than 0.05 taken to be statistically significant. Time to discontinuation of breastfeeding will also be compared between groups graphically using Kaplan-Meier curves, and statistically using the logrank test. Mothers still breastfeeding at the time of data collection will be treated as censored observations. The rates of breastfeeding failure (defined as discontinuation of breastfeeding before the infant is 6 months old) will be compared between mothers of infants admitted to the hospital with jaundice and randomized to the control group, and those in the community as per the breastfeeding rates determined by the Infant Care Survey37 using Pearson’s chi-squared test. Poisson regression models will be used to compare the number of re-hospitalizations for jaundice, hospitalizations for non-jaundice related causes, as well as physician encounters (emergency room visits, community pediatricians / family physicians) in both groups of patients throughout their first 6 months of life. Fisher’s exact test will be used to compare the proportion of mothers in each group seeking breastfeeding help once discharged from the hospital.

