**4.3 Eligibility Criteria**

***Inclusion Criteria***

-Mothers of infants admitted during the study period with hyperbilirubinemia, breastfeeding at the time of admission (any amount of breastfeeding)

-Mothers of infants < 1 month of age at the time of admission

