**4.5 Randomization and Allocation Concealment**

After enrollment, the patients will be randomly allocated to one of the two treatment groups. The randomization schedule will have been previously generated using a computer. Randomization will be blocked with randomly chosen block lengths of 4 or 6. Treatment assignments will be written on a piece of paper and concealed in sequentially numbered opaque envelopes kept in a secure locked location in the study research office. The PI and analyst will be blinded to the treatment intervention, but the lactation consultant and research assistant in charge of assessing eligibility and allocation will not because of the nature of the experimental intervention, which consists of meeting with a lactation consultant.

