**4.7 Study Measurements:**

Baseline information about the infant and the infant’s mother will be recorded at the time of study enrollment. Information about the mother will include language spoken (French or English), maternal age, number of children prior to the participating infant, number of previously breastfed children, maternal education level, household income, marital status, maternal smoking history during pregnancy and after delivery, type of health care provider who followed the pregnancy, attendance at pre-natal classes. Information about the infant will include age, birth weight, gestational age at birth, weight on admission, weight on discharge, need for IV therapy during the hospitalization, septic work up done on admission, antibiotic treatment, length of stay, and the need for formula supplementation before admission, as well as during hospital stay (see Appendix 6).

Follow-up measurements will be collected until the infant is six months of age. Mothers will be given a booklet upon discharge from the hospital, where they will be asked to record the information on formula introduction, solid food introduction, timing of return to work, number of daily formula feeds and sessions at the breast at different points in time, number of hospitalizations and reason, number of visits to primary care physicians and reason, discussion with primary care physician regarding breastfeeding, number of visits to breastfeeding support (see Appendix 6).

A second research assistant, blinded to group allocation, will phone the participating mothers 1 week after discharge from the hospital to remind them to fill out their booklet, and to collect information regarding breastfeeding and formula feeding. Other phone calls will be placed again when the infant is 2, 3, 4 and 6 months old, to remind the mothers to fill out their booklets. The research assistant will also collect the same information the women are asked to record in their booklet, as a back up method in case the booklets are lost or not appropriately filled out. The research assistant will also remind the families, at the beginning of the phone call, not to disclose whether they were allocated to the control or to the study group so that the research assistant can remain blinded.

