**4.8 Outcomes:**

***Primary:*** The primary outcome measured will be exclusive breastfeeding at 3 months, or 3 months corrected if the infant was born prematurely. Exclusive breastfeeding is defined as no other milk intake than maternal milk. Health benefits have been demonstrated after as little as two weeks of exclusive breastfeeding50. However, a larger number of studies have reported positive health outcomes after two to four months of exclusive breastfeeding27, 50-52. Exclusive breastfeeding was chosen as primary outcome as it is a quantifiable measure. Partial breastfeeding is more difficult to define as it may range from very little breastfeeding to almost exclusive breastfeeding, which would have an impact on the magnitude of benefits imparted by breastfeeding. Breastfed babies will be defined as babies who receive no other milk than breast milk, whether directly from the breast or as expressed breast milk.

***Secondary:*** All measurements will be collected at corrected age if infant was born prematurely. 1) Exclusive breastfeeding at six months; 2) Partial breastfeeding at three months; 3) Partial breastfeeding at six months; 4) Number of re-hospitalization for jaundice in the first six months of life; 5) Number of re-hospitalization for non-jaundice related causes in the first six months of life; 6) Number of physician encounters in first 6 months of life; 7) Number of mothers seeking breastfeeding help; 8) Amount and type of breastfeeding support given by child’s primary physician in first six months of life

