# 5. ANALYSIS

**5.1 Sample size:**

In our previous study of infants hospitalized for jaundice, the rate of exclusive breastfeeding at 3 months was roughly 50%17. However, we expect that rate to be lower given the reasons stated above (high level of education in the study population). Moreover, higher levels of education have been shown to be associated with higher rates of participation in different types of study53-55, making the selection bias hypothesis even more likely. Nevertheless, to be conservative we picked 50% as the rate of exclusive breastfeeding at 3 months.

Based on a systematic review of interventions to promote breastfeeding, a 25% increase in the rate of breastfeeding at 3 months is plausible18. In that meta-analysis of randomized controlled trials combining educational and support programs, breastfeeding rates in the short term increased by 36% (95% CI 22-49%), putting our 25% increase estimate at the low end of the confidence interval. This would result in an additional one in four women breastfeeding. An informal survey of hospital based consultant pediatricians confirms this as a clinically significant increase. Setting the probability of type I error at 0.05, a sample size of 58 mothers per group would result in a power of 80% to detect such an increase.

The anticipated number of patients lost to follow-up for the primary outcome is low given that our population of interest consists of young infants. Previous studies in such young children conducted at CHEO have high follow-up rates when primary outcomes were determined through phone follow-up56,57. As a result, we expect a loss to follow-up of no more than 7.5%. To account for this, we would therefore need to recruit 62 patients in each group (Appendix 9).

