**Appendix 5**

**Nomogram for treatment of hyperbilirubinemia**

**Appendix 6**

**Data collection form**

**Patient Study Number:______________**

Language most comfortable with:

English

French

Mother’s age

Mother’s education level

Elementary school / some high school

Completed high school

Vocational / technical training (post high school)

Some university training

Completed university

Household income

Under 30 000$

From 30 000$ to 70 000$

From 70 000$ to 100 000$

Above 100 000$

Declined to answer

Maternal smoking at home

Yes

No

If yes, how much?

Does anyone else smoke at home?

Yes

No

Mother’s marital status

Married / common-law

Single

How many children prior to patient?

How many breastfed children prior to patient?

Did you seek breastfeeding support with these infants?

Who followed the pregnancy?

Obstetrician

Family physician

Midwife

Other (specify)

No prenatal care

Attendance at prenatal classes?

Yes

No

Will mother go back to work before child is one?

Yes

No

If yes, when?

Baby’s age at admission to CHEO?

Baby’s birth weight?

Gestational age at birth?

Baby’s weight on admission to CHEO?

Baby’s weight on discharge from CHEO?

Urine culture done?

Yes

No

Blood culture done?

Yes

No

Cerebrospinal fluid culture done?

Yes

No

Antibiotic therapy given?

Yes

No

Intravenous fluids given?

Yes

No

Duration & volume of fluid given before weaned off

Duration of phototherapy in hours

Length of hospital stay in days

Need for formula supplementation while in hospital?

Yes

No

Formula given prior to hospitalization?

Yes

No

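### The primary test makes no use of pre-admission formula, a plausible predictor already on the data form; stratifying the test on it would add a modest amount of power and protect against chance imbalance

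*Protocol*

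**What the plan says.** - **Primary outcome (section 4.8):** "The primary outcome measured will be exclusive breastfeeding at 3 months, or 3 months corrected if the infant was born prematurely".
- **Primary test (section 5.2):** the method named is the exact test of Fisher, two-sided at the 0.05 level, introduced by the words "The primary analysis will be a comparison between groups of breastfeeding rates at 3 months using". No stratified or adjusted comparison of the primary outcome is described. The only stated use of the baseline data is descriptive summary.
- **Entry (section 4.3):** infants "breastfeeding at the time of admission (any amount of breastfeeding") qualify; only those fed formula alone are excluded. The trial can therefore include infants who had already received formula.
- **Data collected:** section 4.7 lists among the baseline information "the need for formula supplementation before admission, as well as during hospital stay", and the form in Appendix 6 asks "Formula given prior to hospitalization" as a Yes/No item.
- **Prognostic value (section 2.6):** the protocol says earlier studies clearly showed that early supplementation leads to breastfeeding failure. It gives no effect size.
- **Randomisation (section 4.5):** "Randomization will be blocked with randomly chosen block lengths of 4 or 6"; no stratification factor is named.
- **Baseline label (section 4.7):** baseline information is to be recorded at enrolment, yet the list also contains formula during the stay, weight on discharge and length of stay.

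**The concern.** Whether an infant had formula before admission is closely related to the endpoint, and by the protocol's own account it should predict it. The primary analysis leaves this information unused. In a trial of 124 mothers two things are at stake: some power, and protection if one arm happens to receive more already supplemented infants. In that case the plan has no prespecified adjusted result, and an adjustment chosen after the imbalance is seen is open to challenge.

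A smaller matter sits in the same list in section 4.7. Formula during the stay, discharge weight and length of stay become known after allocation. The in-hospital consultation of section 4.6 can affect them, so they are not baseline values.

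**Working it through.** **Inputs from the protocol.** Control rate 50% ("to be conservative we picked 50% as the rate of exclusive breastfeeding at 3 months", section 5.1); intervention rate 75% (a 25-point increase, described there as one additional woman in four); two-sided alpha 0.05; 58 per group analysed; 62 per group recruited.

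**Inputs assumed.** The protocol gives neither the share of infants with prior formula nor its association with the outcome. I take a share of 30% or 50%, and an odds ratio (OR) against exclusive breastfeeding at 3 months of 1, 2, 3, 5 or 8.

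**1. The plan's own figure.** Pooled-variance formula without continuity correction:

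n = [1.960·√(2·0.625·0.375) + 0.842·√(0.5·0.5 + 0.75·0.25)]² / 0.25²
= (1.342 + 0.557)² / 0.0625 ≈ 57.7, so 58 per group.

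This reproduces the stated 58, with power 80.2% by the same approximation. All nine figures in Appendix 9 also reproduce. The formula belongs to an unadjusted chi-square test, not to Fisher's test.

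**2. Power of the two unadjusted tests at 58 per group.** By enumerating all pairs of binomial outcomes:
- Fisher's exact test: 74.3%, with actual type I error 3.2% when both rates are 50%.
- Unadjusted chi-square: 79.9%.

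The gap of 79.9 − 74.3 = 5.6 points is due to the exact test alone and has nothing to do with prior formula.

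**3. Power with stratification on prior formula.** Simulation with 20,000 trials per scenario, 58 per arm, overall rates held at 50% and 75%, a common treatment odds ratio, and unstratified randomisation:

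| Assumed OR | Control rate without / with prior formula (share 50%) | CMH power (share 30% or 50%) | Gain over chi-square |
|---|---|---|---|
| 1 | 50% / 50% | about 80% | 0 |
| 2 | 59% / 41% | about 81% | about 1 point |
| 3 | 63% / 37% | about 82–83% | about 2–3 points |
| 5 | 69% / 31% | about 85% | about 5 points |
| 8 | 74% / 26% | about 87–88% | about 8 points |

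Fisher's test stays at 74–75% throughout. Type I error is 4.8 to 5.3% for CMH and 3.1 to 3.4% for Fisher. If prior formula has no effect, nothing is lost against the chi-square test.

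**4. Chance imbalance at 62 per arm.** From two independent binomials, the probability that the arms differ in prior formula by 10 points or more is 20% (share 30%) to 24% (share 50%); for 15 points or more it is 6 to 9%.

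**5. What such an imbalance does.** With a share of 50%, a 10-point imbalance moves the crude difference by about 0.10 × (59 − 41) = 1.8 points at OR 2, and 0.10 × (74 − 26) = 4.8 points at OR 8. The standard error of the primary difference is √[(0.25 + 0.1875)/58] = 8.7 points, so the shift is roughly 0.2 to 0.55 standard errors. When the intervention arm has at least 10 points more infants with prior formula, Fisher's power falls to about 66%, 61%, 55% and 50% at OR 2, 3, 5 and 8, while CMH stays at 80 to 87%. That unfavourable direction is half of the probability in step 4, about 10 to 12%.

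**The case against.** An unadjusted 2×2 test is a transparent and legitimate primary analysis. Randomisation makes it unbiased, and its type I error already allows for chance imbalance. Supportive adjusted analyses are often left to a statistical analysis plan, which is not at hand. All of this stands. It limits the point to efficiency and robustness; it does not remove it, because the protocol itself fixes the primary test.

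Several stronger readings are tempting, and the documents do not support them:

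- **That the whole gap between Fisher's test and the stratified test is the cost of ignoring prior formula.** It is not: 5 to 6 points belong to the conservative exact test, which is a separate mismatch with the sample-size formula.
- **That a material imbalance is likely.** A 20 to 24% chance is not rare, but it is well short of likely.
- **That prior formula is the baseline value of the outcome.** One Yes/No item cannot separate a single supplement from sustained mixed feeding, and the diary in Appendix 4 allows for formula being stopped again. It is a plausible predictor of unknown strength.
- **That the trial will adjust away part of its effect through post-allocation items.** Section 5.2 plans only descriptive summaries of baseline characteristics. What remains is a wrong label in section 4.7.
- **That randomisation should have been stratified.** That adds at most about 1 further point of power for the stratified test. It would also require two series of envelopes, including those left on the wards at weekends (section 5.4).

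**Conclusion.** The point holds as a modest, low-cost improvement. The planned test is valid, but it leaves unused a recorded item that the protocol itself links to breastfeeding failure. Stratifying on it is worth about 1 to 3 points of power if the predictor is moderate (OR 2 to 3) and about 5 to 8 points if it is strong (OR 5 to 8), measured against an unadjusted chi-square test. Against the planned Fisher's test the total gain is about 7 to 13 points. In the less common trial where the intervention arm draws more supplemented infants, the protection is considerably larger. All covariate figures rest on an assumed share of 30 to 50% and assumed odds ratios. The Fisher and chi-square figures rest only on the protocol's rates and sample size.

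**What to change.** In section 5.2, before any outcome data are compared by arm:

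- Make the primary comparison a Cochran-Mantel-Haenszel test of exclusive breastfeeding at 3 months, stratified by formula before admission (yes/no).
- Report it with a stratified risk difference and 95% confidence interval.
- Keep Fisher's exact test as a supportive analysis.

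In section 4.7, label formula during the stay, discharge weight and length of stay as post-allocation measures and list them apart from baseline.

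The cost is analysis wording only. No new data, no change to the sample size and no change to the randomisation are needed. The drawback is a slightly less simple primary analysis to explain.

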**2.2 Benefits of breastfeeding**

Breastfeeding is preferred for all infants, and exclusive breastfeeding of infants is recommended for the first 6 months after birth1,20-22. The benefits of breastfeeding to both infant and mother are well known and include superior nutritional content of human breast milk, enhanced immunologic status of the newborn, strengthening of the infant-mother dyad, delayed return of ovulation, and economic savings1.

Research has shown that human milk feeding decreases the incidence of multiple illnesses including bacterial meningitis23,24, bacteremia24,25, diarrhea26-29, respiratory tract infection29-31, otitis media26,32,33, and urinary tract infections34,35. A recent study conducted in Spain36 showed that exclusive breastfeeding lowered the risk of hospitalization as a result of infectious diseases during the first year of life. In that study, each additional month of exclusive breastfeeding would have avoided 30% of hospital admissions. A meta-analysis of 33 studies examining healthy infants in developed nations showed similar results, with formula-fed infants experiencing a tripling in severe respiratory illnesses compared with those who were exclusively breastfed for 4 months30. Based on these results, breastfeeding promotion can lead to important economical gains from a societal perspective.

According to the most recent Ottawa Public Health Survey37, breastfeeding rates in the general population are as follows: 91% of women initiate breastfeeding, with 56% practicing exclusive breastfeeding (no fluids other than breast milk). At 3 months, 71% of women continue to breastfeed, with 50% doing exclusive breastfeeding. This number drops to 60% for any breastfeeding at 6 months, with 39% of women exclusively breastfeeding.

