**2.3 Breastfeeding in hospitalized children**

Published reports15 have shown that previously established patterns of breastfeeding are hard to maintain once an infant is hospitalized. Moreover, as mentioned, evidence suggests that mothers of infants admitted to the hospital with jaundice experience guilt16, as well feelings of failure and inadequacy15 as they often feel responsible for the child's admission to hospital. Maternal confidence has been shown to be a strong predictor of breastfeeding duration38,39, with lack of confidence in breastfeeding skills leading to a higher likelihood of weaning in the first six weeks post-partum39. There is only one study in the literature examining the rates of breastfeeding in the jaundiced population17, which was done by the PI of this current study. Surveys were sent to all mothers of eligible infants admitted with jaundice to the Children's Hospital of Eastern Ontario (CHEO) over a 2.5 year period. One hundred and twenty-eight (64%) out of the 200 eligible mothers returned a completed survey. Of those, 92% had a post-secondary education. Information was collected, retrospectively, on length of breastfeeding after discharge from the hospital. Length of breastfeeding for hospitalized infants was compared to that of the Ottawa population, as reported by the City of Ottawa Public Health survey37 in 2005. Although numbers were the same between the jaundiced group and the City of Ottawa group, it is likely that the high education level of the study participants falsely elevated the rate of breastfeeding in the jaundiced infants. As mentioned, 92% of study participants had completed a post-secondary education, as compared to 53% of women involved in the population-based survey. Given that previous reports have shown that women with lower levels of education are more likely to discontinue breastfeeding early38, it is reasonable to postulate that for comparable levels of education, mothers of infants admitted to the hospital with jaundice discontinue breastfeeding earlier than women in the general population.

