***Exclusion criteria***

-Mothers of infants admitted with hyperbilirubinemia who are exclusively formula-fed

-Mothers of infants with hyperbilirubinemia of the predominantly conjugated type as this is a different disease, not associated with breastfeeding difficulties

-Mothers of infants with anatomical abnormalities, such as cleft lip or palate, as this would interfere with breastfeeding and require more intensive intervention.

-Mothers of neurologically impaired infants as breastfeeding may be more difficult in this population

-Mother of infants who were admitted to the NICU after birth and never went home as they are likely to have other comorbidities affecting feeding.

-Mothers of infants feeding via naso-gastric, naso-jejunal, or gastric tube

-Mothers of infants > 1 month of age

-Mothers who have had breast surgery in the past

-Foster mothers or adoptive mothers

-Mothers who do not understand English or French

-Mothers of infants that are the result of multiple birth (eg twins)

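### The control-versus-community comparison sets mothers who were all breastfeeding at admission against survey rates that appear to include women who never started, and does not address education

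*Protocol*

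**What the plan says.** The first secondary objective (Protocol section 1.2) is to compare the rate of breastfeeding failure in control mothers with that in the general population. Section 5.2 defines the outcome: "The rates of breastfeeding failure (defined as discontinuation of breastfeeding before the infant is 6 months old". One side of the comparison is "mothers of infants admitted to the hospital with jaundice and randomized to the control group"; the other is "those in the community as per the breastfeeding rates determined by the Infant Care Survey37". The test is Pearson's chi-squared. No restriction of the survey population and no adjustment is named.

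Section 4.3 admits mothers who are giving any amount of breast milk when their infant, under one month old, is admitted. It excludes "Mothers of infants admitted with hyperbilirubinemia who are exclusively formula-fed".

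Section 2.2 reports the survey: "91% of women initiate breastfeeding, with 56% practicing exclusive breastfeeding (no fluids other than breast milk". It then gives 71% for any breastfeeding at 3 months, and continues: "This number drops to 60% for any breastfeeding at 6 months, with 39% of women exclusively breastfeeding".

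Section 2.3 describes the investigators' earlier study, which was compared with the same survey. It found similar rates, and the protocol attributes this to education: "92% of study participants had completed a post-secondary education, as compared to 53% of women involved in the population-based survey". Maternal education is recorded at baseline in the present trial (section 4.7, Appendix 6).

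**The concern.** The two sides of the test are not selected in the same way. A mother who never started, or who stopped before her infant was admitted, cannot be in the control group. The survey percentages, read as section 2.2 words them, include both kinds of mother as not breastfeeding. That raises the community failure rate and flatters the control group.

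Education may push the same way. Section 2.3 says that a better-educated sample probably inflated the earlier comparison, and the planned test has no means of dealing with this if it happens again.

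At stake is whether the trial can show what sections 2.6 and 8 say it will: how often mothers of jaundiced infants stop early, and whether they are at particular risk. Both distortions would hide an excess of discontinuation.

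**Working it through.** **The plan's own figures.** The protocol gives no sample size or power for this comparison. The primary sample size (50% versus 75%, two-sided 0.05, 80% power) reproduces at 58 per group with the pooled-variance formula and no continuity correction. With 62 recruited and 7.5% lost, 62 × 0.925 = 57.35, so about 57 controls are evaluable.

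**Step 1: the denominator.** Inputs from section 2.2: 91% start; 60% do any breastfeeding at 6 months. Assumption: both are percentages of all women.

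- Failure among all women: 1 - 0.60 = 40.0%.
- Failure among starters: 1 - 0.60/0.91 = 1 - 0.659 = 34.1%.
- Gap: 40.0 - 34.1 = 5.9 points.
- Standard error with 57 controls: √(0.34 × 0.66 / 57) = 0.063, or 6.3 points. The gap is about 0.94 of a standard error.

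The 34.1% still counts mothers who stopped before the usual admission age. Removing them would lower the benchmark further and widen the gap; the documents give no figure for this.

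**Step 2: effect on the planned test.** Normal approximation, 58 controls. The survey size is not given, so its rate was taken as fixed and also as estimated from 500, 1000 or 2000 women; the ranges cover these cases.

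Worked case, fixed survey rate, controls identical to starters: SE under the benchmark = √(0.40 × 0.60 / 58) = 0.0643; SE at the true rate = √(0.341 × 0.659 / 58) = 0.0622. The probability of significance in the direction of less failure is Φ((-1.96 × 0.0643 + 0.0593) / 0.0622) = Φ(-1.07) = 0.14.

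| True control failure | Result | Against 40% | Against 34.1% |
|---|---|---|---|
| 34.1% (same as starters) | significant, controls better | 13-14% | 2.5% |
| 44.1% (10 points worse) | significant, controls worse | 9-10% | 33-37% |
| 49.1% (15 points worse) | significant, controls worse | 27-30% | 61-67% |

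**Step 3: education.** The documents give the imbalance in the earlier study, 92 - 53 = 39 points, but not how strongly failure depends on education. Assume that the imbalance recurs in full and that failure is 5 to 30 points higher without post-secondary education. The bias is then 0.39 × 5 = 2.0 points to 0.39 × 30 = 11.7 points, in the same direction as step 1.

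**Step 4: can standardisation repair it?** If 92% recurs, 0.08 × 57 = 4.6, so about 5 controls lack post-secondary education, yet they would carry 1 - 0.53 = 47% of the weight. Assume 34% failure in both strata.

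- Standardised, 52 and 5 mothers: 1.96 × √(0.53² × 0.2244/52 + 0.47² × 0.2244/5) = 0.207. With 52.4 and 4.6 mothers the result is about 0.215.
- Unstandardised: 1.96 × 0.063 = 0.123.

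The 95% interval is about ±21 to 22 points instead of ±12.

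**The case against.** **The denominator is not stated.** Failure is defined as stopping, and a woman who never started cannot stop, so the definition read literally points to starters. The survey is not at hand either. If its 6-month figure is already among starters, dividing by 0.91 would correct twice. This stands in part. A reader might infer that the protocol commits itself to counting women who never started; it does not. But it points to the survey's rates without restriction, and its wording of them reads most naturally as per all women. The survey must therefore be checked before any number is written in.

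**Education need not repeat itself.** A reader might infer that section 5.1 predicts the same skew in this trial. It uses education and study participation to explain the earlier study's rate, and expects a lower rate here. The settings differ too: 64% returned a retrospective survey (section 2.3), while 80% bedside consent is assumed (section 5.4). This stands: recurrence is possible, not predicted.

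**A worsening over the earlier study cannot be shown.** A reader might also infer that this trial adds a new bias to the old one. The earlier study's eligibility rules are not described fully enough to tell whether the denominator problem was already present.

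**The comparison is weak anyway.** Even against 34.1%, a 10-point excess is detected only 33-37% of the time. This is true, and it favours an estimate with an interval over a significance test. It does not justify a benchmark that is off by about one standard error.

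**Conclusion.** The point holds for a secondary, non-randomised comparison. Section 5.2 fixes an unadjusted test between groups selected differently. If the survey rates are per all women, the benchmark is 5.9 points too high for mothers who had started, and more for mothers still breastfeeding at the age of admission. This takes failure to mean stopping any breastfeeding. The table in the working rests further on 58 controls and the assumed survey sizes.

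The education bias is a possibility in a known direction; its size, 2.0 to 11.7 points, is entirely conditional on the assumptions stated. It would go too far to call a null result uninterpretable: it would be biased towards missing an excess and imprecise, but an interval against a suitable benchmark would still inform. The randomised comparison at 3 months is not touched.

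**What to change.** Amend Protocol section 5.2 as follows.

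1. Confirm with the survey report or its holder what the 6-month percentage is a percentage of. If it is all women, use the rate among those who started (about 34% failure at 6 months) as benchmark. If the holder can supply the rate among mothers still breastfeeding at an infant age matched to admission, use that instead. State the denominator in the text.
2. Replace the chi-squared test by the difference between control group and benchmark with a 95% confidence interval, labelled as a descriptive, non-randomised comparison.
3. Add education-stratified or education-standardised results as a sensitivity analysis only. First map the Appendix 6 categories (vocational training, some university, completed university) to the survey's post-secondary category. State beforehand that the interval could be about ±21 to 22 points if few controls lack post-secondary education.

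The cost is one enquiry about the survey and a little analysis of data already collected. No further mothers, visits or data items are needed. What is given up is a p-value for this objective.
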